### Demographic measures

Demographic measures include gender, age, marital status, country of birth, years lived in the United States, language(s) spoken in the home, ethnicity (Hispanic or not), race, employment status, education, household composition, income, and participation in food assistance programs.

### Potential mediating variables

Knowledge of Fruit and Vegetable Intake: Two questions adapted from previously published questionaires [79–81] are included in the baseline and follow-up surveys to assess knowledge of the appropriate amount of fruits and vegetables an adult should eat. We modified the response categories from servings to cups to be consistent with national dietary guidelines and the NCI screener. The questions are: “How many cups of fruit do you think someone your age should eat each day to have a healthy diet?” and “How many cups of vegetables do you think someone your age should eat each day to have a healthy diet?”

Fruit and Vegetable Availability: Twenty (20) questions regarding F&V availability are included in the baseline and follow-up surveys. These questions were modified from the “Home Environment Survey” [82] to include additional culturally-desired ethnic F&V such as plantains, mangoes, yucca, etc. The questions read as follows: “How often are (type of F&V) available in your home?” Responses range on a five-point Likert scale from never to always.

Barriers to Eating More Fruits and Vegetables: Seven questions to assess barriers to eating more F&V are included in the baseline and follow-up surveys in the form of a statement. Participants are asked to choose how much they agree or disagree with each statement. Responses range on a five-point Likert scale from agree a lot to disagree a lot. The specific barriers queried were drawn from previous studies [55, 83–86] and from our own formative research and include: lack of knowledge regarding how to prepare F&V; lack of time to shop and prepare F&V; high cost of F&V; lack of access to stores selling F&V; F&V spoil too quickly and family preferences.

Perceived Benefits/Outcome Expectations: Two questions regarding perceived benefits/outcome expectations associated with eating more F&V are included in the baseline and follow-up surveys with responses ranging on a five-point Likert scale from agree a lot to disagree a lot. The specific questions are: “You are helping your body by eating more F&V.” and “You may develop health problems if you don’t eat enough F&V.”

Self-Efficacy for Fruit and Vegetable Intake: Six questions are drawn from the Townsend F&V Inventory [87, 88] to assess self-efficacy regarding F&V intake and included in the baseline and follow-up survyes. Responses are on a five point Likert scale and range from agree a lot to disagree a lot. The questions are: “Do you feel you can: eat more F&V as snacks; buy more F&V the next time you shop; plan meals or snacks with F&V; eat 2 or more servings of F&V with dinner; plan meals with more vegetables; and add extra vegetables to casseroles or stews.”

Stage of Change for Fruit and Vegetable Intake: Two questions to assess readiness to eat and readiness to buy more F&V were adapted from previous instruments [83, 89–92] and included in the baseline and follow-up surveys. Participants are asked to select the statement that best described them. Responses included: ‘You are not thinking about”, “You are thinking about”, You are definitely planning to”, “You are trying to” and “You are already eating or buying more F&V”. The responses correspond to these stages of change: pre-contemplation, contemplation, preparation, action and maintenance.

Social Support for Fruit and Vegetable Intake: Four questions regarding social support for F&V intake were adapted from previous research, [93] and included in the baseline and follow-up surveys. The first three questions are: “During the past three months, how often did your friends, family or household members encourage you to: 1) buy F&V; 2) eat F&V; and 3) serve your family more F&Vs. The last question is “During the past three months, how often did your friends, family or household members buy F&V for your household?”. Responses ranged on a five-point Likert scale from never to very often.

Importance of Buying/Eating more Fruits and Vegetables: Two questions regarding the importance of buying and eating more F&V were adapted from previous research [93] and included in the baseline and follow-up surveys. We adapted these questions to ask, “How important is it to you to buy more F&V?” and “How important is it to you to eat more F&V?” Responses range on a five-point Likert scale from not at all important to extremely important.

### Data analysis

To evaluate potential differences between groups that may have occured by chance in the random assignment process, demographics will be assessed by group using chi squared tests for categorical data and analysis of variance for continuous data. Also, group differences in baseline values for outcomes and mediators will be assessed using ANOVA models. To assess characteristics of the baseline F&V intake and mediators, outcomes and mediator variables will be assessed by demographic categories using ANOVA models. To examine F&V intake, mixed-model analysis of variance using SAS PROC MIXED will be used to account for a potential cluster effect within each housing site. All analyses will be performed using SAS version 9.4 (SAS Institute, Cary, NC).

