## Methods

### Overview of study design

All study activities occur at housing sites in Providence County, Rhode Island. Pre-intervention focus groups were conducted with housing complex residents (from non-study sites) to inform intervention development. A total of 15 subsidized housing complexes were recruited into the evaluation cohort. One smaller housing complex served as a pilot site for the intervention group and the remaining fourteen demographically-matched sites were randomized into either the intervention or control group. Adult residents from each housing site were recruited for the evaluation cohort prior to randomization. The multicomponent intervention lasts one year and includes baseline, 6 and 12 month follow-up surveys as well as extensive quantitative and qualitative process evaluation throughout the course of the study. Participants are given a $30 gift card incentive upon completion of each of the three surveys ($90 total). All study protocols were approved by the Brown University Institutional Review Board and all participants provided verbal informed consent. A detailed description of the intervention and evaluation follows.

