### Eligibility criteria for housing sites

In order to participate in the study, the housing complex needed to have: at least 190 units; a relatively low turnover rate (<20 %); a community room or center where surveys, markets and other intervention activities could occur; a willingness to be randomized into one of the two experimental conditions, support the study activities for the duration of the study and help Brown research staff recruit and hire an on-site Resident Assistant. In addition, at least 90 % of the residents needed to be able to speak and read either English or Spanish.

Housing sites were recruited into the study in pairs, matched by number of units, type of site (family or elderly/disabled) and race/ethnicity. The first seven participating sites were Providence Housing Authority sites. The next four sites were Pawtucket Housing Authority Sites and the last four sites were Woonsocket Housing Authority Sites. Nine sites were elderly/disabled housing sites and six were family sites.

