### Randomization

After baseline surveys were completed at each matched pair of sites, the Brown Data Manager assigned the sites to either the intervention or control group using a random number generating function in Excel. *See Fig.**1**for the Live Well Viva Bien study flow diagram.*

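### The baseline comparisons of the arms use chi-squared tests and ANOVA with no site term although sites were randomised in matched pairs, so their p-values are too small and answer no useful question

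*Protocol article*

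**What the plan says.** The Data analysis section of the protocol article sets out three baseline analyses and one outcome analysis.

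- **Demographics by arm:** "demographics will be assessed by group using chi squared tests for categorical data and analysis of variance for continuous data". The stated purpose is "To evaluate potential differences between groups that may have occured by chance in the random assignment process".
- **Baseline outcomes and mediators by arm:** "group differences in baseline values for outcomes and mediators will be assessed using ANOVA models".
- **Baseline associations:** "outcomes and mediator variables will be assessed by demographic categories using ANOVA models".
- **F&V intake:** "mixed-model analysis of variance using SAS PROC MIXED will be used to account for a potential cluster effect within each housing site".

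Only the last of these mentions site.

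The design is described elsewhere in the article. Under Eligibility criteria for housing sites: "Housing sites were recruited into the study in pairs, matched by number of units, type of site (family or elderly/disabled) and race/ethnicity". Allocation followed, pair by pair: "After baseline surveys were completed at each matched pair of sites" (Randomization). Under Overview of study design: "Adult residents from each housing site were recruited for the evaluation cohort prior to randomization". Sample size considerations gives 7 sites per condition plus a pilot site, a target average of at least 107 enrolled per site, and an ICC of 0.01 in a projection based on F&V screener change scores.

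**The concern.** A standard chi-squared test or one-way ANOVA assumes that every resident is an independent observation. Here 14 sites were allocated, and residents of one site share a building type, a city and a neighbourhood. If residents of a site resemble each other at all, the arm difference varies more over repeated randomisations than the test assumes, and small p-values appear too often. The same section uses a mixed model with a site effect for intake, which makes it natural to read the baseline tests as having none.

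There is a second problem, independent of the first. The tests are meant to detect chance differences after random assignment. Residents were recruited and surveyed before their sites were allocated, so among the 14 randomised sites there is no other source of difference. Even a correctly sized test would tell the reader nothing about whether the randomisation worked.

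At stake is the baseline table. Readers use it to judge comparability, and spurious significant results there would cast unwarranted doubt on the trial.

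**Working it through.** **Plan's own figure.** The article gives no error rate for the baseline tests, so there is none to reproduce. The ICC comes from the power projection (8 sites per arm, 75 per site, SD 2.5, difference 0.50 cups, 80% power). There the design effect is 1 + (75 − 1) × 0.01 = 1.74 and the standard error 2.5 × √(2 × 1.74/600) = 0.190. A cluster t-test on 14 df gives 80.3% power one-sided at 5% and 68.6% two-sided. Sidedness is not stated. This confirms that 0.01 is usable as an ordinary between-site share of variance; the power question itself is separate.

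**Inputs.**
- From Sample size considerations: k = 7 randomised sites per arm, m = 107 residents per site, ICC = 0.01.
- Assumed: that this ICC applies to baseline variables; a two-sided 5% level; ρ, the correlation of the site means within a pair, tried at 0, 0.5 and 0.9.

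**Formula.** With total variance σ², the true variance of the arm difference is (2σ²/k) × [ICC(1 − ρ) + (1 − ICC)/m]. A test without a site term uses 2σ²/(km). The ratio of the two is

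VR = (1 − ICC) + m × ICC × (1 − ρ),

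and the actual rejection rate is 2 × [1 − Φ(1.96/√VR)].

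**At ICC 0.01.**
- ρ = 0: VR = 0.99 + 1.07 = 2.06; 1.96/√2.06 = 1.366; rate 17.2%.
- ρ = 0.5: VR = 0.99 + 0.535 = 1.525; rate 11.2%.
- ρ = 0.9: VR = 0.99 + 0.107 = 1.097; rate 6.1%.

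**Range over assumed ICCs.**

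| ICC | ρ = 0 | ρ = 0.5 | ρ = 0.9 |
|---|---|---|---|
| 0.005 | 11.3% | 8.1% | 5.6% |
| 0.01 | 17.2% | 11.2% | 6.1% |
| 0.02 | 26.7% | 17.1% | 7.3% |
| 0.05 | 43.5% | 30.3% | 10.8% |
| 0.10 | 56.5% | 43.3% | 16.3% |

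VR falls to 1 only when ρ = 1 − 1/107, about 0.99.

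**Simulation check** (7 v 7 sites of 107, ICC 0.01, ρ = 0). ANOVA rejected 17.6% of the time and chi-squared 17.3%. A t-test on the site means (12 df) rejected 5.2% and 5.1%. With ρ = 0.5 that unpaired site-level test became conservative (2.7%), so a test worth keeping should use the pairs.

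**Number of flags.** The article lists about 24 baseline variables: 13 demographic, 3 F&V measures and 8 mediators. If the ICC were 0.01 for all of them, the expected number significant would be 24 × 0.172 = 4.1 with ρ = 0, 24 × 0.112 = 2.7 with ρ = 0.5 and 24 × 0.061 = 1.5 with ρ = 0.9, against 24 × 0.05 = 1.2 for a valid test.

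**Outcomes and mediators by demographic category.** This is a different case, because most categories vary among residents of the same site. The variance inflation is roughly 1 + 106 × ICC(category) × ICC(outcome). With an outcome ICC of 0.01 and a category ICC of 0.1 it is 1.106, a rate of about 6%. With 0.01 and 0.3 it is 1.318, about 9%. With 0.05 and 0.3 it is 2.59, about 22%. Simulations with these values gave somewhat lower rates of 5.5%, 7.2% and 16.5%. All these ICCs are assumptions.

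**The case against.** **Matching.** The pairs were matched on number of units, site type and race/ethnicity, which are the features most likely to make demographics cluster. Variation shared by a pair cancels from the arm contrast. This stands, and it is why the rates at ρ = 0 are upper values for their ICC. It reduces the inflation without removing it, short of near-perfect matching.

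**Borrowed ICC.** The 0.01 belongs to F&V change scores, not to age, ethnicity or mediator scores at baseline. This also stands. The 17% is conditional on it. Demographics may well cluster more, since nine sites are elderly/disabled and six are family sites, but the article gives no figure.

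**Not explicit.** The article does not say that clustering is ignored at baseline. That is inferred from the named tests and from the contrast with the intake model. It is the natural reading, and the tests are a stated choice rather than a detail left out.

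**No consequence for efficacy.** The intake analysis allows for site, and nothing in the article selects covariates from the baseline tests or treats a significant one as failed randomisation. A reader might infer that the tests will drive the adjustment or undermine the primary result. The document does not support that.

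**Conclusion.** The point holds as a limited one. As written, the baseline arm comparisons give anti-conservative p-values. If the ICC of 0.01 carried over, a nominal 5% test would reject about 17% of the time without a matching effect, 11% with within-pair correlation 0.5, and 6% with 0.9. Higher ICCs would raise these rates and closer matching would lower them. The tests also ask a question that the order of enrolment, survey and randomisation has already answered for the 14 randomised sites. The harm is a misleading account of baseline comparability.

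Two stronger readings are tempting and should be resisted. One is that the tests are bound to flag imbalances. At ICC 0.01, even without matching, a given variable goes unflagged about 83% of the time (100 − 17.2). The other is that the analyses by demographic category are equally affected. Their inflation depends on how strongly both the category and the outcome cluster by site, and for the same outcome ICC it is smaller than for an arm comparison.

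**What to change.** 1. Replace the between-arm significance tests with descriptive summaries by arm, at site and at resident level, with standardised differences.
2. If a test is kept, make it a site-level comparison that uses the matched pairs, such as an analysis of the within-pair differences in site means.
3. For baseline outcomes and mediators by demographic category, use the random-site mixed model already planned for F&V intake.

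The cost is a few sentences in the analysis text and a revised table shell. No data, sample size or software changes are needed.

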### Sample size considerations

The original sample size projections showed that ending the study with 75 participants in each of 16 housing complex sites (8 sites per condition) using reasonable estimates of the intraclass correlation (0.01) and Standard Deviation 2.5 (based on our previous studies), we would be able to detect an effect size of 0.50 cups (based on F&V Screener change scores) between experimental groups with 80 % power. We originally planned to recruit 16 sites but dropped our sample size slightly (7 sites in each condition and 1 pilot site = 15 sites) because of large budget cuts from NCI at the beginning of the funding period. We anticipated retention at 75 % or greater of the original sample so aimed to enroll an average of at least 107 participants at each of the 15 housing sites.

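### The trial is sized on change scores and no baseline covariate is stated; if change scores are analysed, adjusting for baseline intake would be more precise at no extra data cost

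*Protocol article*

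**What the plan says.** Data analysis gives one sentence on the outcome model: "mixed-model analysis of variance using SAS PROC MIXED will be used to account for a potential cluster effect within each housing site". It does not state the form of the dependent variable, the fixed effects or any covariates.

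The same section does say what happens to baseline outcome and mediator values. They are compared between groups with ANOVA, to look for differences left by chance in the assignment, and they are described across demographic categories. No adjustment for such a difference is stated.

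Sample size considerations fixes the scale used for planning: "detect an effect size of 0.50 cups (based on F&V Screener change scores) between experimental groups with 80 % power", "using reasonable estimates of the intraclass correlation (0.01) and Standard Deviation 2.5 (based on our previous studies"). That was for "ending the study with 75 participants in each of 16 housing complex sites (8 sites per condition"). The number of sites was later reduced to "7 sites in each condition and 1 pilot site = 15 sites".

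Intake is measured at baseline, 6 and 12 months (Abstract; Overview of study design), and sites are assigned after the baseline surveys at each matched pair are complete (Randomization). A pre-randomisation value of the outcome is therefore collected by design.

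**The concern.** A change score subtracts the whole baseline value, including its measurement error. When the correlation between baseline and follow-up is well below 1, as is plausible for short self-report intake screeners, this over-corrects. A group that starts high by chance then tends to show a smaller change through regression to the mean. With only 14 randomised sites, a chance difference between arms in mean baseline intake is quite possible. Testing for that difference does not remove it; putting baseline in the model does.

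Precision is also at stake. The stated power belongs to 16 sites and 14 were randomised, so a gain from data already in hand is worth having. Regression on baseline is, in large samples, never less efficient than analysing change.

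**Working it through.** **Inputs from the article.** Detectable difference 0.50 cups; SD 2.5, taken as the SD of the change score; ICC 0.01; originally 8 sites per arm with 75 completers each; now 7 randomised sites per arm; enrolment of at least 107 per site and 75 % retention, so m = 107 × 0.75 = 80.25 completers per site.

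**Assumptions, not in the article.** Two-sided 5 % test (alpha and sidedness are not given); t test on between-site df, ignoring the pairing; baseline-to-follow-up correlation r from 0.4 to 0.7; equal variances at both times.

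**1. The article's own figure (8 × 75).** Design effect = 1 + 74 × 0.01 = 1.74. SE = 2.5 × √(2 × 1.74/600) = 0.190.
- Two-sided 5 %: power is 74.7 % by the normal approximation and 68.6 % by t on 14 df.
- One-sided 5 %, t on 14 df: 80.3 %.

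The stated 80 % is therefore met under the last convention and not under the two-sided ones. As the convention is not stated, this is not called an error here.

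**2. Change-score power for the randomised design (7 × 80.25).** Design effect = 1 + 79.25 × 0.01 = 1.7925; completers per arm = 561.75. SE = 2.5 × √(2 × 1.7925/561.75) = 0.200. Two-sided t on 12 df: **63.3 %**.

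**3. Gain from baseline adjustment.** With a common variance s² at both times:
- Var(change) = 2s²(1−r)
- Var(baseline-adjusted) = s²(1−r²)
- Ratio f = (1−r²)/(2(1−r)) = (1+r)/2, so the reduction is (1−r)/2.

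**4. Carrying it to the arm comparison.** At ICC 0.01 and m = 80.25, the between-site share of the variance of a site mean is 0.8025/1.7925, about 45 %. Individual-level adjustment need not reduce that share. Two cases bound the result:
- (a) both components fall by f: variance factor f × 1.7925;
- (b) only the within-site part falls: variance factor 0.99f + 0.8025.

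| r | individual-level cut | (a) power | (b) total cut | (b) power |
|---|---|---|---|---|
| 0.4 | 30 % | 78.4 % | 17 % | 71 % |
| 0.5 | 25 % | 75.6 % | 14 % | 70 % |
| 0.6 | 20 % | 72.9 % | 11 % | 68 % |
| 0.7 | 15 % | 70.3 % | 8 % | 67 % |

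Example for r = 0.4. (a) 0.7 × 1.7925 = 1.255, SE 0.167. (b) 0.99 × 0.7 + 0.8025 = 1.4955, SE 0.182.

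**5. Effect of a chance baseline imbalance.** If the SD of change is 2.5, the SD at each time is 2.5/√(2(1−r)): 2.28 for r = 0.4 and 3.23 for r = 0.7. Assuming a baseline ICC of 0.01 as well, the SE of the baseline difference between arms is 0.182 and 0.258 cups. A change-score analysis carries (1−r) of an imbalance into the estimate. A one-SE imbalance therefore shifts the estimate by 0.6 × 0.182 = 0.11 cups (r = 0.4) or 0.3 × 0.258 = 0.08 cups (r = 0.7), which is 22 % or 15 % of the 0.50-cup target. The shift is conditional on the imbalance that occurs; it averages to zero over randomisations.

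**The case against.** The strongest objection is that a reader might infer from Data analysis that the primary model is unadjusted. The article does not say so. Its one sentence names a model class, the software and the handling of site. It does not even name the arm term, so it is not a full specification. PROC MIXED can take baseline as a covariate or as a repeated measure, and a fuller plan, not shown, may do either. Likewise, a reader might infer that correlation between a participant's repeated measurements is ignored because only site is mentioned. Accounting for site does not imply that, and the article does not describe the within-person structure. Neither reading is part of this point.

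Two further objections stand in part. First, change scores appear only in the sizing, and a sizing basis is not the analysis model; the comparison above therefore holds only if change scores are what is analysed. Second, r is nowhere in the article, and an even fall in both variance components is the favourable case. In case (b) the gain in power over 63 % is roughly half or less of that in case (a).

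What the objections do not remove is this. The article plans on change scores, assigns the baseline values to a between-group test, and states no adjustment. They make the gain conditional and smaller; they do not reverse it.

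**Conclusion.** The point holds in conditional form. If change scores are analysed, regressing follow-up intake on baseline is the better method. It cuts individual-level variance by (1−r)/2, which is 15–30 % for an assumed r of 0.7–0.4. At 7 v 7 sites, power for 0.50 cups goes from about 63 % to 70–78 %, or only to 67–71 % if between-site variance is untouched. It also protects the estimate from a baseline imbalance that 14 sites can easily produce. These figures depend on the assumed r, equal variances at both times, SD 2.5 being the SD of change, ICC 0.01, and a two-sided 5 % t test on 12 df. They do not show that the trial's analysis is wrong; they show that the method as described leaves an available gain unclaimed.

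**What to change.** State in Data analysis that the primary model regresses follow-up fruit and vegetable intake on arm and individual baseline intake, with a random site effect and small-sample (for example Kenward-Roger) or between-site degrees of freedom. Adding the site-mean baseline is optional; it is aimed at the between-site variance that individual adjustment may leave. If a fuller plan already specifies baseline adjustment, one sentence saying so is enough. The baseline comparison between groups can stay as description, but it should not stand in for adjustment. The cost is wording only: baseline intake is already collected, and no change to design, recruitment or follow-up is needed.

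### Sites are matched and randomised in pairs, but the stated model names only a site cluster effect; adding site type would protect efficiency at almost no cost

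*Protocol article*

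**What the plan says.** Under Eligibility criteria for housing sites, the protocol article states: "Housing sites were recruited into the study in pairs, matched by number of units, type of site (family or elderly/disabled) and race/ethnicity". The same section gives nine elderly/disabled and six family sites. They entered by housing authority: seven in Providence, then four in Pawtucket, then four in Woonsocket.

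Under Randomization, allocation is pair by pair: "After baseline surveys were completed at each matched pair of sites, the Brown Data Manager assigned the sites" to one arm or the other. Fourteen sites were randomised. A fifteenth, smaller site served as a pilot for the intervention and was not randomised (Overview of study design).

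Under Data analysis, one sentence covers the outcome model: a mixed model fitted in PROC MIXED "to account for a potential cluster effect within each housing site". It names no pair term and no matching factor, but it does not list the model terms either.

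Under Sample size considerations, the inputs are "ending the study with 75 participants in each of 16 housing complex sites (8 sites per condition"), "intraclass correlation (0.01) and Standard Deviation 2.5", and a target difference of 0.50 cups in change score. No allowance is made for matching.

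**The concern.** Matching forces the two arms to agree on the matched factors, so differences between pairs cancel out of the arm contrast. A model with only a site effect does not know this. It estimates its between-site error from all differences among sites within an arm, including those between family and elderly/disabled sites. If these kinds of site change by different amounts, the estimated standard error exceeds the true one. The test then rejects less often than its nominal level under the null, and the interval is wider than the design warrants.

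With only 14 randomised clusters, efficiency is scarce. The trial has paid for the matching when recruiting sites, and the analysis as described does not clearly collect the benefit.

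**Working it through.** **Inputs from the article.** SD 2.5 cups, ICC 0.01, difference 0.50 cups, 75 completers per site; 8 sites per arm in the original plan, 7 per arm randomised. **Assumptions.** Two-sided 0.05 (no level is stated), equal site sizes, analysis of site means, exact matching on type. With nine elderly/disabled and six family sites in all, exact matching makes the randomised sites 8 and 6, that is 4 and 3 pairs.

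**1. The plan's own figure.** Design effect = 1 + 74 × 0.01 = 1.74. SE = 2.5 × √(2 × 1.74 / 600) = 0.190. Power is 74.7 % by the normal approximation and 68.6 % by t on 14 df, so the stated 80 % does not reproduce. That is a separate matter, but it shows there is no slack. With 7 sites per arm, SE = 2.5 × √(2 × 1.74 / 525) = 0.2035, and power is 69.0 % (normal) or 61.7 % (t, 12 df).

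**2. Variance of a site mean.** Between-site variance = 0.01 × 6.25 = 0.0625. Sampling variance = 0.99 × 6.25 / 75 = 0.0825. The total is 0.145, and √(2 × 0.145 / 7) = 0.2035, as above.

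**3. Site type uninformative.** Adjustment moves from 12 to 11 df with the same SE: power goes from 61.7 % to 61.0 %.

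**4. Types differ by an assumed 0.25 cups in change.** Type then contributes variance 0.25² × (3/7) × (4/7) = 0.0153, about a quarter (0.0153 / 0.0625 = 24 %) of the planned between-site variance.
- *Added to the planned site variance.* The adjusted model keeps SE 0.2035 on 11 df, power 61.0 %. The site-only model has expected error variance 0.145 + 0.0153 × 7/6 = 0.163, and its interval is about 5 % wider. By simulation (400,000 runs) it has size 3.9 % and power 57.1 %.
- *Total held at plan.* Residual variance is 0.145 − 0.0153 = 0.1297, SE = √(2 × 0.1297 / 7) = 0.1925, adjusted power 65.8 %. The site-only model has simulated size 3.8 % and power 61.6 %.

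The gain is about 4 points either way.

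**5. Full paired analysis (6 df).** Simulated at 7 pairs, 75 per site, ICC 0.01, by the share of between-site variance lying between pairs:

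| Share | Site-only size | Site-only power | Paired power |
|---|---|---|---|
| 0 | 5.0 % | 61.7 % | 54.0 % |
| 0.25 | 4.0 % | 62.2 % | 58.5 % |
| 0.45 | 3.2 % | 62.7 % | 62.8 % |
| 0.5 | 3.1 % | 62.9 % | 64.1 % |
| 1 | 1.5 % | 64.7 % | 77.4 % |

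Break-even is at a share of about 45 %. At an assumed ICC of 0.03 it comes earlier: at a share of 0.25, paired power is 38.7 % against 37.4 %.

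**6. Random pair term.** With one site per arm in each pair, a positive estimated pair variance puts the arm contrast on the within-pair error with 6 df, as fixed pairs would. Only when that variance is estimated at zero do the degrees of freedom revert to about 11 or 12. An approximate simulation of this switching gave a type I error of 5.4 to 6.6 %.

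**The case against.** The strongest reply is that the article never excludes the pairing. Its one sentence on the model does not even list arm, time or baseline, and a fuller plan may carry the matching factors. A reader might infer that the analysis ignores the pairs; the text supports only the narrower statement that site is the one design feature it names. That much stands, and the point is worded accordingly. It remains useful because allocation is built on factors that appear nowhere in the described analysis, and the remedy is one specific term.

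A reader might also infer that power is certainly lost, or lost heavily. The documents do not support this. They give no between-pair variance and no difference in change between site types. Large losses arise only if site variance is set above the planned ICC. A 0.5-cup type difference, for example, equals the whole target effect. Nor can a seasonal imbalance between pairs be argued, since the article gives the order of housing authorities but no start dates.

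Finally, leaving pairs out of a small matched trial is a recognised choice, because a paired analysis halves the degrees of freedom. That is correct, and it is why a full paired model is not proposed as primary. It does not count against a single 1-df term for site type.

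**Conclusion.** The point holds as one of efficiency. Randomisation is within pairs matched on factors likely to matter, and the described model names only the site. To the extent that those factors predict change in intake, tests are conservative and intervals too wide. Type I error stays at or below 5 %, so validity is not in question.

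The size cannot be fixed from the documents. Under the assumptions shown, adjusting for site type risks about 1 point of power and gains about 4 if the two kinds of site differ by 0.25 cups; the gain grows with the difference. A full paired analysis is not clearly better: at ICC 0.01 it costs about 8 points if matching is uninformative and gains power only if pairs explain roughly 45 % or more of the between-site variance.

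**What to change.** - In Data analysis, add site type (family v elderly/disabled) as a fixed effect in the PROC MIXED model of the 14 randomised sites. The cost is one sentence and 1 of 12 df.
- Prespecify the analysis of the 7 within-pair differences (6 df) as a sensitivity analysis.
- Do not make a random pair term with data-dependent df the primary model, since with 7 pairs it can be mildly anticonservative.
- State that the unpaired, non-randomised pilot site has no place in the pair-based analysis.
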